#### Support

The researcher will offer personal training (averaging 30 min) to the experimental group to help its members download and install the App onto their mobile phones, demonstrate the usage of each module of the BCS, and help the women write an introductory message in the Discussion forum and ask a question in the Ask-the-Expert forum.

Technical assistance will be available via email or telephone from 8:00 am to 5:00 pm from Monday to Friday. At other times, users can email a technical assistant or leave a message on voicemail. A technical assistant will check emails and voicemail messages five days a week and respond to the women as soon as possible.

#### Fidelity of the intervention

Different strategies will be used to enhance the fidelity of the BCS, such as maintaining consistency in the delivery of the intervention and monitoring and reinforcing the women’s adherence to the intervention. To maintain consistency in the delivery of the intervention, the same researcher ([name]) will organise the topics, give feedback and verbal cues, and provide encouragement and suggestions in the Discussion forum to the women regarding their progress with symptom management. The frequency and duration of the logins will be monitored to evaluate the women’s adherence. The women’s questions will be answered by health care professionals within 24 h to improve adherence to the BCS program.

#### Comparison

The women in both the experimental and control groups will receive routine care provided by the hospital. Routine care involves support from doctors and nurses during the two-day hospitalisation for each cycle of chemotherapy. Before treatment commences, a nurse will provide information on chemotherapy and possible side effects. There are currently no IIPs for education and social support provided by health care services at the study sites. The control group may freely use the internet to search for information about breast cancer. However, they will not have access to the BCS program.

### Outcome measures

#### Primary outcomes

##### Stanford Inventory of Cancer Patient Adjustment (SICPA)

Self-efficacy will be measured using the Stanford Inventory of Cancer Patient Adjustment (SICPA) [28]. The SICPA is a 38-item instrument assessing patients’ beliefs in their ability to manage cancer-related problems. Higher total scores equate to a higher level of self-efficacy. The SICPA has demonstrated good psychometric properties [28]. The SICPA has been translated into Chinese and validated in patients with cancer. The Chinese version of the SICPA has Cronbach’s alpha reliability coefficients of 0.95 [29].

##### Multidimensional Scale of Perceived Social Support (MSPSS)

Social support will be evaluated using the Multidimensional Scale of Perceived Social Support (MSPSS) [30]. The MSPSS is a 12-item self-report instrument assessing the respondent’s perceptions of support from three sources: family, friends and a significant other. A mean score greater than 5 indicates good support, a score of 3 to 5 indicates moderate support, and a score of less than 3 indicates poor social support. The original MSPSS has good reliability and validity [30]. The MSPSS has been translated into Chinese and validated in a Chinese population. The Chinese version of the MSPSS has adequate internal consistency (Cronbach’s α = 0.92) and construct validity [31].

### Secondary outcomes

#### M.D. Anderson symptom Inventory (MDASI)

Symptom distress will be assessed using the M.D. Anderson Symptom Inventory (MDASI) [32]. The MDASI consists of a 13-item symptom scale and a 6-item interference scale. A mean score of 1 to 4 indicates mild symptom distress, 5–6 indicates moderate symptom distress, and 7–10 indicates severe symptom distress. The original MDASI has demonstrated good reliability and validity [32]. The MDASI has been translated into Chinese and used in Chinese patients with cancer. The Chinese version of the MDASI has Cronbach’s alpha reliability coefficients of 0.74 and 0.88 for the symptom subscale and interference subscale, respectively [29].

#### Functional Assessment of cancer treatment-B (FACT-B, version 4)

Quality of life related to breast cancer will be measured using a Chinese version of the Functional Assessment of Cancer Treatment-B (FACT-B) [33]. FACT-B is a 37-item instrument assessing the impact of breast cancer and chemotherapy on dimensions of QoL. A higher total score means a better QoL. The English version of FACT-B has demonstrated good reliability and validity for women with breast cancer [34]. FACT-B has been translated into Chinese and has been widely used to assess the QoL of Chinese patients with different types of cancer. The Chinese version of FACT-B has a Cronbach’s alpha reliability coefficient of 0.87 for the entire scale [35].

#### Hospital anxiety and depression scale (HADS)

Anxiety and depression will be assessed using the Hospital Anxiety and Depression Scale (HADS) [36]. The HADS is a 14-item instrument assessing depression and anxiety in a medical setting. Higher total scores indicate greater distress. The original HADS has shown good reliability and validity in breast cancer survivors [37]. The HADS has been translated into Chinese and is widely used in the Chinese population with different types of health conditions. The Cronbach’s alpha coefficients of the Chinese version of HADS are 0.806 and 0.724 for the anxiety and depression subscales, respectively [3].

### Other outcomes

#### Satisfaction with care

Women’s satisfaction with their care during chemotherapy will be assessed with a six-item checklist developed for this study. Questions such as “Overall, how satisfied are you with the care so far?” will be rated on a five-point Likert scale, with 1 meaning “not at all” and 5 meaning “very much”. For each subscale, higher scores indicate greater satisfaction (Additional file 1).

#### Internet usage data for the BCS

The website contains a tracking system. Internet usage data, such as the frequency and duration of logins and the website activity of each module of the BCS, will be recorded and evaluated.

#### Demographic and clinical data

The data collected will include the women’s age, marital status, highest education level, employment status, monthly family income and BMI. Disease-related information will be provided by the hospital when the women are recruited; such information will include breast cancer stage, types of surgery, comorbidities and postoperative complications.

### Participant timeline

This study began recruiting participants in May 2016, and the primary endpoints (baseline and post-test 1) and follow-up measure (post-test 2) are expected to be completed in February 2017. The Consolidated Standards of Reporting Trials (CONSORT) flowchart is presented in Fig. 3 [38].

**Fig. 3 Fig3:**
[figure not shown]
CONSORT flowchart of the study - adapted from Schulz et al. [38]. Note: SICPA: Stanford Inventory of Cancer Patient Adjustment; MSPSS: Multidimensional Scale of Perceived Social Support; MDASI: M.D. Anderson Symptom Inventory; FACT-B: Functional Assessment of Cancer Treatment-B; HADS: Hospital Anxiety and Depression Scale

### Sample size

The primary outcome of self-efficacy will be used to estimate the effect size based on power analysis [39]. A previous study on IIPs for women with breast cancer that measured QoL, social support, and health competence reported a medium effect size (0.46); however, the effect size for self-efficacy was not mentioned [40]. Similar research on psychoeducation to enhance the self-efficacy of Chinese patients with colorectal cancer also demonstrated a medium effect size of 0.60 for self-efficacy [29]. We estimate a 20% attrition rate based on a dropout rate of 10–15% in previous studies involving IIPs [27, 40]. To achieve a power of 0.80 at a 0.05 level of significance, a minimum of 108 women (54 in each group) are required for this study.

### Recruitment

Recruitment will take place before the women begin chemotherapy. The physician will introduce the BCS to women who meet the inclusion criteria and will provide the women with the contact details of the research assistant (RA). Women that have contacted the RA will be approached by the RA at the oncology unit to provide them with additional information regarding the BCS and to answer any questions that they might have. Women who verbally agree to participate will be followed up to obtain their written consent. The enrolment period is expected to extend over a 6-month period. Data will be collected before randomisation (baseline), immediately after the intervention (post-test 1), and 12 weeks after the intervention (post-test 2). The women will be rewarded with a small gift (equal to RMB 30) for each questionnaire completed.

### Randomisation

For each hospital, the Research Randomizer [41] will be used to generate a random set of 27 unique, non-duplicating numbers from 1 to 54. Different coloured slips (pinks slips for randomly generated numbers, white slips for all other numbers) will be put into an opaque envelope. The participants that pick a pink slip from the opaque envelope will be assigned to the experimental group; the others will be assigned to the control group. The women in the intervention group will have access to the BCS program and receive routine care while undergoing treatment. The women in the control group will receive routine care during treatment. The health care providers and the RA collecting the data will be blinded to the participants’ group allocation.

### Data analysis

All outcome measures will be analysed using IBM SPSS Statistics 21.0 [42]. An intention-to-treat analysis will be adopted to manage missing data. The baseline differences between the intervention and control groups will be assessed using the chi-square (χ^2^) test for binary demographic data and the independent sample t-test for continuous variables. Adjusted for possible confounding factors of demographic variables, the repeated measures triply MANCOVA will be conducted to determine whether the BCS intervention is effective in improving self-efficacy, social support and QoL and for reducing symptom distress, anxiety and depression across three time points of data collection (baseline, post-test 1 and post-test 2). The independent t-test will be used to compare how satisfied the experimental group and the control group are with the care that they received during chemotherapy 12 weeks after intervention.

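### Intention-to-treat is named as the missing-data method, but the one effectiveness analysis, a three-visit MANCOVA, is complete-case unless scores are imputed, and no imputation is named

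*Protocol article*

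**What the plan says.** Three sections of the protocol article bear on this.

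- **Data analysis.** Missing data are covered in one sentence: "An intention-to-treat analysis will be adopted to manage missing data". No imputation, likelihood-based model or other method is named. For effectiveness, "the repeated measures triply MANCOVA will be conducted to determine whether the BCS intervention is effective". This single model takes in both primary outcomes and all the secondary ones, adjusts for demographic variables, and has baseline and both post-tests in it. On software: "All outcome measures will be analysed using IBM SPSS Statistics 21.0".
- **Sample size.** "We estimate a 20% attrition rate". The total is 108 women, 54 per arm, for power 0.80 at the 0.05 level. Self-efficacy is the outcome used, and an effect of 0.60 is cited from a related study.
- **Participant timeline.** The visits are ranked: "the primary endpoints (baseline and post-test 1) and follow-up measure (post-test 2"). Post-test 1 therefore carries the primary comparison, and post-test 2 is follow-up.

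**The concern.** Intention-to-treat answers two questions: which women are in the analysis, and in which arm each is counted. It supplies no value, likelihood or assumption for an unobserved score. The article does not merely pass over missing data; it names a device that cannot do the job.

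The named model then works against the label. A repeated-measures multivariate linear model needs each woman's whole outcome vector and all her covariates. Run on raw data, it removes a woman if any one of these is absent. Because the primary and follow-up visits sit in the same model, a missed follow-up questionnaire also takes a woman's complete post-test 1 data out of the primary comparison.

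What is at stake is whether the main result compares the randomised groups or only those women who completed everything.

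**Working it through.** **Inputs.** From the article: 108 women randomised 1:1, 20% attrition, effect 0.60 SD, power 0.80, alpha 0.05, five instruments, three visits. Assumed: a two-sided test (not stated), the timing of dropout, and any rate of scattered missing scores. Listwise deletion is a known property of the method, not something the article states. Power below is for a two-group comparison of one outcome, as in the sample size section, not for the MANCOVA itself.

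**1. The plan's own figure.** Normal approximation: n per arm = 2 × (1.96 + 0.842)² / 0.60² = 43.6, so 44. Inflation: 44 / 0.80 = 55 per arm, 110 in total. With the exact t-test, n is 45 per arm, and 45 × 1.2 = 54 per arm gives exactly 108. (45 / 0.80 = 56.25, so 57 per arm, would give 114.) The figure of 108 is reproduced, and it already budgets for 20% loss.

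**2. Scores needed per woman.** 5 instruments × 3 visits = 15. With HADS split into anxiety and depression, 6 × 3 = 18.

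**3. Complete cases at planned attrition.** 108 × 0.80 = 86.4 women, 43.2 per arm. Power = Φ(0.60 × √(43.2 / 2) − 1.96) = Φ(0.83) = 0.796; by t-test, 0.787. That is about one point below the target.

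**4. Post-test 1 records discarded.** Loss by post-test 2 is held at 20%; loss by post-test 1 is varied, because the article does not give it. Power is by normal approximation.

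| Lost by post-test 1 (assumed) | Women with post-test 1 | Complete cases | Records discarded | Power if post-test 1 records kept | Power, complete cases |
|---|---|---|---|---|---|
| 5% | 102.6 | 86.4 | 16.2 | 0.86 | 0.80 |
| 10% | 97.2 | 86.4 | 10.8 | 0.84 | 0.80 |
| 15% | 91.8 | 86.4 | 5.4 | 0.82 | 0.80 |
| 20% | 86.4 | 86.4 | 0 | 0.80 | 0.80 |

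The t-test gives values about one point lower (0.83 against 0.79 in the 10% row).

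**5. Scattered missing scores among retained women (assumed rates).** If each score is missing independently:

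- 1% per score: 86.4 × 0.99^15 = 74, or 86.4 × 0.99^18 = 72
- 2% per score: 86.4 × 0.98^15 = 64, or 86.4 × 0.98^18 = 60

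Scores from one visit tend to be missing together. If they always are, only three visits count: 86.4 × 0.99³ = 84 and 86.4 × 0.98³ = 81. The range is therefore wide: 72 to 84 women at 1%, and 60 to 81 at 2%.

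**6. Direction of bias.** Two illustrations, both built on assumptions, point opposite ways.

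- *Inflation.* If the 20% who leave the app arm had no benefit and the rest gained 0.60 SD, the effect in all randomised women is 0.8 × 0.60 + 0.2 × 0 = 0.48. Completers show 0.60, and 0.60 / 0.48 = 1.25.
- *Attenuation.* In a simulation of 600 trials of 108 women, the true effect was 0.60 SD and between-visit correlations were 0.5 to 0.6. About 24% were lost after post-test 1, more often those with low post-test 1 self-efficacy. The baseline-adjusted post-test 1 effect averaged 0.53 in completers and 0.59 in all women seen.

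**The case against.** The strongest reply is that complete-case analysis is inferred, not stated. A reader might infer that the protocol prescribes listwise deletion; it does not. The sentence on missing data suggests a wish to keep incomplete cases, and imputation followed by the MANCOVA would fit both statements. A full protocol or analysis plan, not shown here, could contain it. This stands as a limit on the claim: the conflict exists only if nothing is imputed. It does not rescue the sentence, which still names a device that cannot handle missing scores.

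A reader might also infer that the effect will be inflated because women who lose interest in the app will drop out. The documents do not support this. They leave the amount of app use to each woman and do not equate stopping the app with leaving the study. Questionnaires are completed separately, with a small gift for each. Nor is the trial simply unblinded: the women know their arm, but the article says that health care providers and the assistant collecting the data do not. Differential dropout is possible; its direction is unknown.

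On power, the sample size already allows for 20% attrition, so the planned loss cannot be presented as a serious shortfall. Any larger loss rests on assumed rates of scattered missing scores, and the independence assumption is the least favourable of those tried.

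Finally, a mixed model is not a full cure. It relies on data being missing at random. If the no-benefit women in the inflation example left before post-test 1, a mixed model could also return about 0.60. This is why a sensitivity analysis is needed. It is also fair to say that replacing the MANCOVA is not the only remedy.

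**Conclusion.** The point holds in a limited form. The sentence on missing data is wrong as written. Unless scores are imputed first, the one named effectiveness analysis conflicts with the intention-to-treat label and lets follow-up attendance decide who counts at the primary visit.

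The planned attrition leaves about 86 of 108 women, with power of about 0.79 at 0.60 SD. The main harm is therefore possible selection bias, whose direction and size the documents do not settle, together with observed post-test 1 data thrown away. Between none and about 16 women would be affected if loss by post-test 1 is between 20% and 5% and total loss is 20%. Scattered missing scores would reduce the analysed number further, by an amount that cannot be fixed from the article.

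The text should be corrected before the data are analysed, because it governs the trial's main claim.

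**What to change.** 1. State that the intention-to-treat set is all randomised women, each in her assigned arm, and keep this separate from the handling of missing scores.
2. Analyse each outcome with a likelihood-based linear mixed model (SPSS MIXED) that keeps all observed scores. Use group, time and group-by-time effects, an unstructured within-woman covariance and the planned demographic covariates. Include baseline, either in the response vector with a mean common to both arms or as a covariate. With baseline in the response vector, a woman with no post-test score still stays in the analysis.
3. An acceptable alternative is multiple imputation before the planned MANCOVA, with the imputation model and the rule for pooling the multivariate tests stated. This keeps the single multivariate test.
4. Add one sensitivity analysis for data missing not at random, for example delta-adjusted imputation.

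The cost is a little extra analysis work, with no new patients or data. The mixed model runs in the software already named; whether the delta-adjusted step does so should be checked. If separate models replace the single multivariate test, the plan should also say which outcomes carry the effectiveness claim.

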### Study setting

This study will be conducted in two university affiliated tertiary public hospitals in the People’s Republic of China. At each participating hospital, an average of 40 women with breast cancer per month receive chemotherapy; approximately 15 of these women have access to the internet. The usual treatment for women with breast cancer at these two participating hospital consists of four cycles of chemotherapy, with each cycle lasting 21 days.

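### Randomisation is stratified by hospital but the stated analyses leave hospital out, which can cost some precision; baseline tests cannot identify confounders, and the covariate set is left open

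*Protocol article*

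**What the plan says.** All references are to the protocol article.

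- **Sites (Study setting):** "This study will be conducted in two university affiliated tertiary public hospitals".
- **Allocation (Randomisation):** "For each hospital, the Research Randomizer [41] will be used to generate a random set of 27 unique, non-duplicating numbers from 1 to 54". The drawn numbers become the experimental slips, so each hospital has its own list with a forced 27:27 split.
- **Main model (Data analysis):** "Adjusted for possible confounding factors of demographic variables, the repeated measures triply MANCOVA will be conducted". It runs "across three time points of data collection (baseline, post-test 1 and post-test 2"), so baseline is one of the repeated responses.
- **What counts as demographic (Demographic and clinical data):** "the women’s age, marital status, highest education level, employment status, monthly family income and BMI". That is six variables, and hospital is not one of them.
- **Baseline (Data analysis):** "The baseline differences between the intervention and control groups will be assessed using the chi-square" test or, for continuous variables, a t-test. This comes just before the adjustment sentence. Nothing says that the results decide which covariates enter.
- **Satisfaction (Data analysis):** "The independent t-test will be used to compare how satisfied the experimental group and the control group are", at 12 weeks after the intervention, with no adjustment.

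**The concern.** When allocation is balanced within hospitals, the arm difference is protected from hospital differences by design. An analysis that ignores hospital still leaves the between-hospital variance in its error term, so the reported standard error is larger than the true one. Intervals are then too wide and power is given away.

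A hospital effect is plausible here. The Comparison section says routine care comes from each hospital's own doctors and nurses at every cycle, after baseline has been measured. Hospital could therefore affect change as well as level. Satisfaction is a rating of that care, taken at one time point.

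The second strand is the basis for adjustment. Under randomisation any baseline difference between arms is due to chance, so testing it cannot show that a variable is a confounder. What makes a covariate useful is that it predicts the outcome. Describing the set only as possible confounders among the demographics leaves it open, and an open set can be settled after the data are seen.

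**Working it through.** **1. The plan's own figure.** The Sample size section cites a study that "demonstrated a medium effect size of 0.60 for self-efficacy", with power 0.80, level 0.05 (two-sided assumed) and 20% attrition.
- Normal formula: 2 × (1.96 + 0.8416)² / 0.60² = 43.6, so 44 per arm. Then 44 / 0.8 = 55 per arm, 110 in total, within 2 of the stated 108.
- The t-test version needs 45 per arm, and 45 × 1.2 = 54, or exactly 108.

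The effect size of 0.60 is therefore the operative input. Nothing below changes this number.

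**2. Cost of leaving hospital out, single time point.** Assume two equal hospitals whose means differ by D within-hospital SDs, with arms balanced in each. Ignoring hospital adds D²/4 to the error variance.
- Ratio of reported to true standard error = √(1 + D²/4).
- True type I error = 2 × [1 − Φ(1.96 × ratio)].

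| D (assumed) | Hospital share of variance | SE ratio | Type I error |
|---|---|---|---|
| 0.5 | 0.0625/1.0625 = 5.9% | 1.031 | 0.043 |
| 1.0 | 0.25/1.25 = 20% | 1.118 | 0.028 |

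**3. Simulation of the same comparison.** Settings: 108 women with no dropout, 27:27 in each hospital, effect 0.60, and 6,000 runs per setting. The hospital share is an assumption.

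| Hospital share | Model SE without → with hospital | Type I error without → with | Power without → with |
|---|---|---|---|
| 1% | 0.192 → 0.191 | 0.053 → 0.053 | 0.871 → 0.873 |
| 5% | 0.192 → 0.187 | 0.049 → 0.056 | 0.872 → 0.884 |
| 10% | 0.192 → 0.182 | 0.038 → 0.047 | 0.875 → 0.896 |
| 20% | 0.192 → 0.172 | 0.028 → 0.051 | 0.895 → 0.929 |

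The simulation error of a 5% rate is √(0.05 × 0.95 / 6000) = 0.003, so the 0.056 is about two simulation errors from nominal. Leaving hospital out makes the test conservative. The effect is negligible at 1% and noticeable from 5% to 10% upwards.

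**4. The repeated-measures model.** Suppose a hospital adds the same amount h to a woman's score at every visit. Her change from baseline is (post + h) − (baseline + h) = post − baseline, and h is gone. A group-by-time test is then unaffected by leaving hospital out. Only a hospital difference in change stays in its error. The figures in steps 2 and 3 apply to between-group effects at one time point, and so most directly to the satisfaction t-test.

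**5. Baseline tests and covariates.** With six independent demographics each tested at 5%, the chance of at least one significant difference is 1 − 0.95⁶ = 0.265, about 26%. Simulation with six covariates, each correlated 0.2 to 0.3 with the outcome (assumed), gave these type I errors:
- adjusting for all six, fixed in advance: 0.042 to 0.054;
- adjusting only for those significant at baseline: 0.037 to 0.042;
- choosing freely among all 2⁶ = 64 subsets after seeing the outcome: 0.14 to 0.23.

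The first two used 3,000 runs and the third 500.

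**The case against.** The strongest reply has four parts.

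- **Condensed article.** A full protocol or analysis plan may list the covariates and name hospital. This stands for the exact covariate list, which is not faulted here for being absent. It carries less weight for hospital. The article states what the adjustment consists of, and it fixes the satisfaction comparison as an independent t-test, which has no place for hospital. A fuller document would have to depart from that text, not just add detail.
- **Validity.** A reader might infer that the trial's standard errors are misstated in a way that threatens its conclusions. The documents do not support this. The error runs one way: standard errors come out too large, so a false claim of benefit becomes less likely. The main model also includes baseline as a response, so a constant hospital difference drops out of a group-by-time test. Both points stand.
- **Size.** Nothing in the article suggests a 1 SD hospital difference. Both sites are university-affiliated tertiary hospitals with the same usual four-cycle treatment. At a 5% share the power gain is about one percentage point. This also stands.
- **Data-dependent model.** A reader might infer from the order of the sentences that the baseline tests choose the covariates and thereby inflate the type I error. The text does not say that they choose. Selection by those tests alone did not inflate the error in simulation. Inflation needed a free choice among subsets after seeing outcomes, which the article does not describe. Nor should the four disease variables be counted to reach 1 − 0.95¹⁰ = 40%, because the adjustment is confined to demographic variables.

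**Conclusion.** The concern holds in a limited form. The stated analyses do not follow the randomisation: allocation is balanced within hospital and hospital appears in neither the main model nor the satisfaction test. The consequence is lost precision, not bias or false positives. For a single-time comparison the standard error is about 3% too large at an assumed hospital difference of 0.5 SD and 12% too large at 1 SD. In a group-by-time test, only a hospital difference in change matters.

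The baseline significance tests serve no purpose in identifying confounders. The adjustment wording permits a data-driven choice of covariates without prescribing one. The 26% is the chance of at least one significant baseline difference, assuming independence; it is not an error rate for the treatment comparison.

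These sizes rest on two equal hospitals, intact 27:27 balance, and hospital differences and covariate correlations that the article does not give.

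**What to change.** - Include hospital as a fixed factor in every between-group analysis, including the repeated-measures MANCOVA.
- Replace the satisfaction t-test with a linear model of arm plus hospital. Satisfaction has no planned baseline value, so no baseline term is needed there.
- Present baseline characteristics by arm descriptively and drop the significance tests.
- Name the demographic covariates in advance, chosen because they are expected to predict the outcome.
- If the baseline score is to be used as a covariate, remove it from the response vector. It should not be both.

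The cost is one degree of freedom for hospital and a short edit to the Data analysis section. Moving baseline from response to covariate is optional and would mean respecifying the model. No new data are needed, and the sample size stays at 108.

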The BCS program is a multi-component intervention that includes a Learning forum, a Discussion forum, an Ask-the-Expert forum, and a Personal Stories forum. Four factors from the self-efficacy theory [21] and the functional and structural social support concepts from the social exchange theory [22] are incorporated into the BCS program. Regarding the self-efficacy theory, mastery experiences include the provision of symptom management knowledge in the Learning forum; vicarious experiences involve reading others’ personal stories in the Personal Stories forum and sharing experiences in the Discussion forum; verbal persuasion comes from feedback and verbal cues from peers and health care professionals in the Discussion forum and Ask-the-Expert forum; and the learning materials and sharing of experiences may modify women’s perceptions of their expected arousal states. In terms of social exchange theory, the Discussion and Ask-the-Expert forums are designed to build structural social networks and provide multiple types of functional support from peers and health care professionals. Figure 1 illustrates the theoretical framework of the BCS.

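### The protocol's sections disagree on the primary test: the trial is sized on self-efficacy alone, but effectiveness is judged by one MANCOVA of all primary and secondary outcomes over three time points

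*Protocol article*

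**What the plan says.** Four parts of the protocol article bear on what the primary test is.

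- **Outcome measures.** SICPA and MSPSS both stand under the primary heading. Symptom distress (MDASI), quality of life (FACT-B), and anxiety and depression (HADS) are secondary.
- **Sample size.** Only one outcome is used, and it is named in the singular: "The primary outcome of self-efficacy will be used to estimate the effect size based on power analysis". The effect cited for it comes from a psychoeducation study that "also demonstrated a medium effect size of 0.60 for self-efficacy". With 80% power, alpha 0.05 and 20% attrition, the section arrives at its target: "a minimum of 108 women (54 in each group) are required for this study".
- **Participant timeline.** Baseline and post-test 1 are called the primary endpoints, and post-test 2 a follow-up measure.
- **Data analysis.** One repeated-measures MANCOVA, adjusted for demographic variables, is run over all three time points "to determine whether the BCS intervention is effective in improving self-efficacy, social support and QoL and for reducing symptom distress, anxiety and depression". No other effectiveness analysis is described, apart from a t-test for satisfaction with care.

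**The concern.** The Data analysis section does not carry through the distinctions made elsewhere. It drops the split between primary and secondary outcomes, the single outcome used for sizing, and the primary time point.

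This matters because a multivariate test asks whether the arms differ on any combination of the outcomes. Rejection could come from anxiety or symptom distress alone, so it cannot answer whether self-efficacy improved, which is the question the 108 women were recruited to answer. Non-rejection is equally hard to read, because the trial was not sized for that test. Readers of the result would then have to decide afterwards which comparison counts as success.

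**Working it through.** **1. Reproduce the stated sample size.** Inputs from Sample size: d = 0.60, power 0.80, alpha 0.05, 20% attrition. Sidedness is not stated; two-sided is assumed.

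- Normal approximation: n = 2(1.96 + 0.842)² / 0.60² = 43.6, so 44 per arm. The t-test needs 45 per arm.
- 45 × 1.2 = 54 per arm, or 108 in total. This is an exact match.
- The other cited effect, 0.46, gives 180 to 190 two-sided, so it is not the basis.
- An average of the two effects (0.53), one-sided, also gives 108, but the protocol states neither the averaging nor a one-sided test.

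The stated number is therefore that of a univariate comparison of self-efficacy. After 20% loss, 54 × 0.8 = 43.2, so 43 per arm. The univariate t-test then has power 0.785.

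**2. Power of the stated type of test if only SICPA moves.** Assumptions, none given in the protocol:

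- Six outcome scores (anxiety and depression counted separately), each with two changes from baseline, giving 12 variables.
- Hotelling's T² stands in for the group-by-time test; demographic covariates are ignored.
- Equal correlation r between time points and equal correlation ρ between outcomes.
- SICPA shifts by 0.60 SD at both post-tests and nothing else shifts.

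Formulas: D² = 0.60² × c(ρ) × 2 / [3(1 − r)], where c(ρ) = (1 + 4ρ) / [(1 − ρ)(1 + 5ρ)], which is 1, 1.257 or 1.714 for ρ = 0, 0.3 or 0.5. The noncentrality is (43/2) × D², referred to F with 12 and 86 − 13 = 73 df.

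Example: r = 0.5 and ρ = 0 give D² = 0.36 × 1 × 1.333 = 0.48, noncentrality 21.5 × 0.48 = 10.32, power 0.454.

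| r over time | ρ = 0 | ρ = 0.3 | ρ = 0.5 |
|---|---|---|---|
| 0.3 | 0.32 | 0.41 | 0.56 |
| 0.5 | 0.45 | 0.57 | 0.74 |
| 0.7 | 0.72 | 0.84 | 0.95 |
| 0.8 | 0.91 | 0.97 | 1.00 |

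If both primaries shift by 0.60 SD at r = 0.5, power is 0.82, 0.86 or 0.95.

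**3. Power of the direct test.** Adjusting SICPA at post-test 1 for its baseline reduces the residual SD to √(1 − r²). The effective size 0.60/√(1 − r²) is 0.629, 0.693 or 0.840 at r = 0.3, 0.5 or 0.7. With 43 per arm, power is 0.82, 0.89 or 0.97. When only SICPA moves, this is above the 12-df test in every cell of the table for those r.

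**4. What an omnibus rejection shows.** Take six variables, 43 per arm, the four secondary scores shifted by 0.6 SD and neither primary shifted. The multivariate test is significant in 95% to 99% of trials, although neither primary has an effect.

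**5. Error rate if each primary were tested at 0.05.** Without any gate, the chance of at least one false positive is 1 − 0.95² = 9.75% if the two are independent, and 9.1% at correlation 0.5. With the omnibus test as a gate (simulated, six variables), a false primary claim occurs in about 2% of trials when nothing differs, and in about 9% to 10% under the scenario of step 4.

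**The case against.** **Alpha control.** A reader might infer that either primary can be claimed at 0.05 with no control. The article does not say so. Testing order and alpha rules are commonly left to a full protocol or analysis plan, which is not shown. The 9% to 10% is conditional on a procedure the document does not describe, and the omnibus test itself holds 5% when no outcome differs. This objection stands, so silence on alpha is not part of the finding.

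**No primary contrast at all.** That would also be too strong. Sample size and Participant timeline together point to SICPA at post-test 1. What remains is that Outcome measures lists two primaries and Data analysis tests everything together.

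**Loss of power.** A reader might conclude that power is necessarily lost. It depends on correlations the protocol does not give and on only SICPA moving. At r of 0.7 to 0.8 the omnibus test exceeds 0.80 in five of six cells. The protocol hypothesises improvement in all outcomes, and if both primaries move, power is 0.82 to 0.95 at r = 0.5. This also stands: a shortfall is possible, not established.

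**MSPSS content.** One might add that the scale asks about family, friends and a significant other while the app offers peers and professionals. Whether users would count forum peers as friends cannot be settled from the text, and it has no bearing on which test is primary. It is not relied on here.

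None of this changes the fact that the stated analysis answers a different question from the one the trial was sized for.

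**Conclusion.** The concern holds as an inconsistency between Outcome measures, Participant timeline, Sample size and Data analysis over what the primary test is. Two parts rest on the text and on logic alone: 108 comes from a univariate comparison of self-efficacy (two-sided, d = 0.60), and a significant MANCOVA over all outcomes would not show an effect on self-efficacy.

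The size of any power loss is conditional. If only SICPA moves, it runs from severe (0.32) to none (0.95) for r between 0.3 and 0.7, under the equal-correlation assumptions above. The documents do not support saying that the trial is underpowered in general or that its false-positive rate is about 10%.

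**What to change.** In Data analysis:

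- Name the baseline-adjusted SICPA difference between groups at post-test 1 as the single primary test, at two-sided 0.05.
- Test MSPSS at post-test 1 only if SICPA is significant, or relabel MSPSS as secondary.
- Analyse each scale in its own model, with estimates and 95% confidence intervals; post-test 2 is follow-up.
- Describe any MANCOVA as supportive only.

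Align the primary outcomes heading with this choice.

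The cost is wording, and 108 women still serve. The downside is that MSPSS cannot be claimed as a primary success if SICPA fails. Splitting alpha (0.025 each, d = 0.60 for both) would keep two co-equal primaries, but it needs 53 to 55 per arm before dropout. Dividing by 0.8 gives 67 to 69 per arm, or 134 to 138 women.
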